## Abstract

**Background:**

Female Genital Mutilation (FGM) is a traditional practice which is harmful to health and is profoundly rooted in many Sub-Saharan African countries. It is estimated that between 100 and 140 million women around the world have been victims of some form of FGM and that each year 3 million girls are at risk of being submitted to these practices. As a consequence of the migratory phenomena, the problems associated with FGM have extended to the Western countries receiving the immigrants. The practice of FGM has repercussions on the physical, psychic, sexual and reproductive health of women, severely deteriorating their current and future quality of life. Primary healthcare professionals are in a privileged position to detect and prevent these situations of risk which will be increasingly more present in Spain.

**Methods/Design:**

The objective of the study is to describe the knowledge, attitudes and practices of the primary healthcare professionals, working in 25 health care centres in Barcelona and Girona regions, regarding FGM, as well as to investigate the perception of this subject among the migrant communities from countries with strong roots in these practices. A transversal descriptive study will be performed with a questionnaire to primary healthcare professionals and migrant healthcare users.

Using a questionnaire specifically designed for this study, we will evaluate the knowledge, attitudes and skills of the healthcare professionals to approach this problem. In a sub-study, performed with a similar methodology but with the participation of cultural mediators, the perceptions of the migrant families in relation to their position and expectancies in view of the result of preventive interventions will be determined.

Variables related to the socio-demographic aspects, knowledge of FGM (types, cultural origin, geographic distribution and ethnicity), evaluation of attitudes and beliefs towards FGM and previous contact or experience with cases or risk situations will be obtained.

**Discussion:**

Knowledge of these harmful practices and a preventive approach from a transcultural perspective may represent a positive intervention model for integrative care of immigrants, respecting their values and culture while also being effective in eliminating the physical and psychic consequences of FGM.

## Background

In the last decades, in Spain and other Western countries there has been a distorted visualisation of the phenomena associated with gender and immigration, especially in the case of sub-Saharan women, their daughters and female genital mutilation (FGM) [1,2]. The polarised reactions that they generate in the society of destination do not help to change the conditions of life and health of the girls but rather their integration is presented in dichotomic terms: assimilation versus stigmatisation or criminalisation [3,4].

The WHO calculates that between 100 and 140 million women and girls in the world have been victims of some kind of FGM. It has also been estimated that each year about three million girls are at risk or are subjected to some kind of ablation, essentially in the 28 countries in sub-Saharan Africa, where this type of ritual has strong, ancestral roots. Since 1952, when the UN Human Rights Commission adopted the first resolution on this matter, most international organizations have spoken out against these harmful traditional practices, encouraging their state members to promote legislative initiatives to eradicate these practices. In spite of all the efforts by international organizations and governments, we are faced with a problem which, as mentioned in a report by the UNICEF Innocenti centre, "continues to be one of the most persistent and omnipresent violations of human rights, and which is also tolerated in silence" [5,6].

FGM is carried out in girls aged between birth (7 days) and pre-adolescence (10-12 years), always before the first menstruation and marriage.

According to the WHO [6] four types of FGM can be distinguished according to the severity of the intervention practised: Type I or clitoridectomy, partial or total removal of the clitoris and/or the prepuce; Type II or excision, partial or total removal of the clitoris and the labia minora, with or without excision of the labia majora; Type III or infibulation, narrowing of the vaginal orifice with creation of a covering seal by cutting and appositioning the labia minora and/or the labia majora, with or without excision of the clitoris. A small hole is left to allow for urinating and menstrual bleeding; and Type IV which includes various practices in the genital area, with a varying degree of severity and without any therapeutic purpose (piercing, dry sex, stretching, cauterising the clitoris, etc).

Types I and II are predominant in Western and Central sub-Saharan African countries, whereas type III is the most common form of FGM in Eastern Africa. It should be specified that not all African countries practice FGM, and neither is it practiced by all the ethnic groups in one and the same country. It is pre-Islamic and is practiced by Muslims, Coptic Christians and Falasha Jews.

The performance of FGM has an impact on the physical, psychic, sexual and reproductive health of women, severely deteriorating their present and future quality of life [7-13].

The social and cultural roots of these practices condition their perpetuation, despite important restrictive legal initiatives having been developed in some countries of origin and destination of the immigrants.

In addition to the many initiatives of the international agencies, who recommend their prohibition (WHO, UNICEF, UNFPA, EU), FGM in any of its forms is considered as a crime of injury in Spain, being described and punished in article 149 of the Penal Code with sentences of 6 to 12 years in prison even if the mutilation has been performed abroad.

On the other hand, the lack of intervention by healthcare professionals to avoid genital mutilation in situations of risk is considered to be a crime of omission of duty to avoid and promote persecution in article 450 of the Spanish Penal Code. This means, for example, that professionals who, in relation to their work activity, are aware of FGM having been performed or of a girl at risk of being submitted to this practice and do not avoid or report the event, are committing a crime which may be punished with a prison sentence.

In Spain, the first cases were detected in Catalonia in 1993 and were discovered and reported by healthcare professionals. These cases were reported and resulted in a verdict of not guilty for the parents of the girls who claimed "no intention to injure and error of prohibition". Since then there is no knowledge of further mutilations having taken place in Spain, although it is known that the families take advantage of their holidays to the country of origin to carry out the initiation of their daughters. In some cases in which the environment of the family of the minor was investigated, the parents declared than FGM had been carried out abroad (in their country of origin) believing that Spanish law could do nothing. The most common form of presentation of the problem associated with FGM in our setting is a comment made by a family with daughters of an age of initiation, concerning an imminent journey to Africa. This situation is mainly detected by healthcare professionals, social services and schools. Judicial actions undertaken in view of knowledge of a journey of girls at risk in their country of origin consist in preventive withholding of the passport and the commitment of the parents to not mutilate their daughters, in addition to an obligatory check up on their return.

In the case of FGM there is a complex interaction between rights, values and cultures which indicate that we can not be limited to only applying punishment. Some of the control measures proposed may harm the intimacy and dignity of the minors to be protected (such as the obligation of undergoing gynaecologic check up until the age of 18) or may lead to a serious family destructuration on withdrawal of the custody of the parents and causing the girls to be admitted under the protection of social services. All of this generates professional doubts and dilemmas with respect to the consequences of intervention (reporting, court intervention, family disintegration and destructuration, criminalization of the parents, possibility of no return of the minors for fear of the legal consequences in the country of destination) or no intervention (professional consequences of omission, irreparable physical and psychic lesions in the girls).

There are few studies in Spain related to FGM in primary care. A previous survey carried out by investigators of our team of healthcare professionals in the county of the Maresme (Barcelona) [14,15] reported that 56% of those surveyed did not correctly identify the typology of FGM, 17% were not interested in the subject and their answer to the question "What would you do in the case of FGM?" was: "ignored". Twenty-one percent of the personnel of the sexual and reproductive healthcare programme, 7% of the paediatricians and 5% of the general medicine professionals declared having detected or known of some case in both mothers and daughters. This study demonstrated the profound lack of knowledge of the healthcare professionals in relation to this subject, raising the need to sensitise and educate from the privileged setting of primary healthcare, where most of the cases or situations at risk are detected. In other European countries the situation is similar [16-18].

The important migratory waves of sub-Saharan populations to the European Union in the last years are shaping societies which are increasingly more complex and diverse. The way to deal with the health problems affecting these people represents a challenge for the healthcare systems [19] and for the professionals working within who must develop approaches to allow transcultural care [20-22].

Based on the production of mapping FGM in Spain, with data of the census and municipal registration, updated in 2005 we have estimated that 3,659 women living in Catalonia have undergone some type of FGM; and 2,189 girls are at risk of having some type of FGM performed in the next years, without taking into account the impact of the last processes of immigration regularisation.

The deep-rooted social and cultural nature of these practices conditions their perpetuation despite the development of important legal restrictive initiatives in some countries of origin and destination of the immigrants. However, when migrant women return to their societies of origin they are points of reference, credibility and recognition in such transcendent aspects as reproductive health and education [23]. These women bear new knowledge acquired in Europe which has been incorporated and put into practice during the migratory process. Thus, the exploration of the beliefs and perceptions of the sub-Saharan immigrants attending our healthcare centres in relation to FGM may be of interest.

In addition to an adequate legislative framework, a preventive standpoint is essential which, with knowledge and sensitisation, will allow healthcare providers to approach the question of FGM and thereby avoid the conflicts brought about by legislation of aspects linked to the privacy and identity of the migrant persons.

Given the accessibility of the population to the universal healthcare available in Spain, primary healthcare may have a key role in the prevention of FGM [24,25], with these professionals being in the first line for dealing with this problem. Interdisciplinary teams with paediatricians, family physicians, nurse, social workers, gynaecologists and midwives, allow an integral approach to the families from the countries of sub-Saharan Africa where the question of FGM is always very present [26,27].

We are not aware of other previous experiences developed in primary healthcare in Spain or in Europe. Several studies have described registries of cases and others have reported knowledge, attitudes and practices related to FGM by professionals of specialised care [28], but to our knowledge there are no publications on these aspects in relation to first level healthcare or to preventive work undertaken from the primary care setting. We therefore developed the present study to provide knowledge and elements for improvement in the approach to FGM to prevent this problem on behalf of the healthcare professionals.

### Objectives

#### Main objectives

1. Describe the knowledge, attitudes and practices of the professionals of the primary healthcare teams related to the practice of FGM and how to approach any of the situations related to this procedure.

2. Know the degree of knowledge the primary care professionals have on the regulatory legislative framework in relation to the FGM and the penal consequences for both the migrant families and the healthcare professionals.

3. Identify dilemmas of ethics and interventions given the hypothetical presentation of a problem related to FGM in any of its presentations (girls at risk, recent FGM, knowledge of intention to perform FGM).

#### Secondary objectives

4. Identify the training needs of the primary care professionals in relation to how to approach FGM.

5. Quantify the frequency of presentation of problems related to FGM in primary care offices.

6. Attempt to approach the position of the immigrant families given the intervention of healthcare agents to avoid these practices.

## Methods/design

This is a transversal, descriptive study based on a survey regarding the knowledge, attitudes and practices (KAP) of the professionals, and users from countries of sub-Saharan Africa versus the performance of FGM. The study will be carried out in the 25 Primary Healthcare Centres from (PHC) Northern Barcelona and the Maresme Region (Barcelona, Spain) and from the counties of Girona (Girona, Spain) providing healthcare coverage to a population of 487,000 inhabitants.

### Study subjects. Sample size and selection method

#### Healthcare Workers

Healthcare providers of the teams of paediatrics, social work, family medicine, nursing and gynaecology-obstetrics associated with the PHC of Northern Barcelona, the Maresme and the counties of Girona.

#### Selection of healthcare providers

The study includes all the professionals of the PHC teams, the Sexual and Reproductive Healthcare Programme and the Departments of Paediatrics and Gynaecology-Obstetrics of the hospital centres. It will also include the social workers linked to PHC. In the Catalonian Healthcare System, primary healthcare professionals work in teams who attend the healthcare needs of the population assigned in a determined territory. These teams are made up of family physicians, general medicine physicians, paediatricians, nurses and social workers. Support programs are available within the setting of sexual and reproductive health and these are mainly constituted by gynaecologists, nurses and midwives. All these healthcare providers will be asked to voluntarily and anonymously participate in filling out the questionnaire.

The target population will therefore be all the healthcare providers of the previously mentioned groups and teams who will be contacted through the heads of the teams and informative sessions in each of the centres and departments. A response rate of around 75% has been estimated, similar to that obtained by the same system in a previous study by our group in 2001 and 2004 [14,15].

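### Hospital paediatrics and gynaecology-obstetrics staff are in the target population, but objectives 1, 2, 4 and 5 concern primary care and the main estimates are not restricted to it

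*Protocol article*

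**What the plan says.** **Who is surveyed.** Besides the primary healthcare teams, the Selection of healthcare providers section includes the Sexual and Reproductive Healthcare Programme and "the Departments of Paediatrics and Gynaecology-Obstetrics of the hospital centres", and adds the social workers linked to the centres. It concludes: "The target population will therefore be all the healthcare providers of the previously mentioned groups and teams". Hospital staff are not set apart.

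**Which setting.** Methods/design says "The study will be carried out in the 25 Primary Healthcare Centres" and names no hospital. The Healthcare Workers paragraph lists the disciplines and ends with "nursing and gynaecology-obstetrics associated with the PHC of Northern Barcelona, the Maresme and the counties of Girona".

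**Which population the objectives name.** Objective 1: "Describe the knowledge, attitudes and practices of the professionals of the primary healthcare teams related to the practice of FGM". Objective 2: "Know the degree of knowledge the primary care professionals have on the regulatory legislative framework". Objective 4 concerns the training needs of primary care professionals. Objective 5: "Quantify the frequency of presentation of problems related to FGM in primary care offices". Objective 3 names no setting.

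**What is analysed.** For objectives 1 and 2, the Analysis plan describes each knowledge and attitude item by means or percentages. It then compares each item by gender, age, professional category and work centre or department. Objectives 3 and 5 are handled in the same way, and objective 4 is drawn from these results. A multiple logistic model relates characteristics of the professionals to correct identification of FGM. None of these steps is limited to primary care respondents.

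**The concern.** The population surveyed is wider than the one that four of the five objectives answered from the professionals' questionnaire name. The Background also justifies the study by a gap in first-level care, set against existing reports from specialised care. If hospital respondents enter the main percentages, a hospital obstetrician's contact with cases counts towards how often the problem presents in primary care offices. The logistic associations likewise become those of a mixed group.

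What is at stake is the interpretation of the headline figures. They would depend partly on how many hospital staff happen to return the questionnaire, a number that the plan neither fixes nor predicts.

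**Working it through.** The professionals' survey has no stated sample size or precision, so there is no figure of the plan to reproduce. The article's one calculated sample size, 191, belongs to the family survey and does not bear on this point.

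**Step 1. Do hospital departments fall within primary care as the article defines it?** The Selection section describes primary healthcare teams as family and general physicians, paediatricians, nurses and social workers. It describes the sexual and reproductive health programmes as support, mainly gynaecologists, nurses and midwives. Hospital departments are in neither description. The mismatch therefore concerns only the hospital departments, not the programme.

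**Step 2. Does another section remove them before the main estimate?** No.
- Sample size and selection: results may be stratified by participation rate in the primary healthcare centres. This is not a hospital/primary-care split.
- Study variables: work centre or department is collected, so a split is possible.
- Analysis plan: that item is used in a bivariate comparison made after the main description.
- Data collection: centres are indexed by a code unrelated to location or to the providing entity. If only that code were kept, hospital and primary care could not be told apart.

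**Step 3. Size.** Let w be the hospital share of respondents, h the hospital rate and p the primary care rate.

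Pooled rate = (1 − w) × p + w × h, so the shift = w × (h − p).

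Neither w nor h is in the article. The nearest figures are those of the team's earlier survey in the Background, for having detected or known of a case: 21% in the sexual and reproductive healthcare programme, 7% of paediatricians and 5% in general medicine. The following is an illustration only. Its assumptions are:
- p: 20% of the principal set are programme staff at 21%, and 80% are others at 6% (midway between 5% and 7%). So p = 0.20 × 21% + 0.80 × 6% = 9.0%.
- h: 7% (like the paediatricians), 21% (like the programme), or 14% (half of each).
- w: 5% to 30%.

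| w | h = 7% | h = 14% | h = 21% |
|---|---|---|---|
| 5% | 8.9% | 9.25% | 9.6% |
| 10% | 8.8% | 9.5% | 10.2% |
| 20% | 8.6% | 10.0% | 11.4% |
| 30% | 8.4% | 10.5% | 12.6% |

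For example, with w = 20% and h = 14%: 0.80 × 9.0% + 0.20 × 14% = 7.2% + 2.8% = 10.0%. Across the table the shift runs from −0.6 points (0.30 × (7 − 9)) to +3.6 points (0.30 × (21 − 9)). Under these assumptions even the sign depends on h. If h = p, the shift is zero.

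**The case against.** The strongest defence is that the plan already contains the remedy. Work centre or department is collected, and every knowledge and attitude item is to be compared across it. In a descriptive survey such a comparison yields group-specific percentages. This stands in part: the data can still answer the objectives. A reader might infer that the study cannot answer objectives 1, 2, 4 and 5 at all, and the article does not support that. But the breakdown does not say which figure is the answer to each objective, and it does not touch the logistic model.

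A second defence is that the choice of analysis set is usually left to a statistical analysis plan, and that no sentence announces a pooled percentage labelled as primary care. The second half is correct. The point, however, does not rest on missing detail: the article states two different populations, and its analysis text, applied as written, uses the wider one.

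A third is that the inclusion is deliberate, since the Selection section plans sessions in centres and departments. That is plausible, and surveying hospital staff is a legitimate choice. The fault lies in the mismatch with the objectives, not in collecting the data.

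A reader might also infer an inflation of 25% to 50%. That comes from giving hospital staff a 21% rate against a 6% baseline: 0.10 × 21% + 0.90 × 6% = 7.5%, and 0.20 × 21% + 0.80 × 6% = 9.0%. The article does not support it. The 21% belongs to the reproductive health programme, which works in support of primary care and stays in the primary care set. No hospital rate is reported, and the hospital departments include paediatrics, for which the only figure is 7%.

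**Conclusion.** The point holds as a mismatch between the target population and the population named in objectives 1, 2, 4 and 5, carried into the main percentages and the logistic model. It does not extend to objective 3, which names no setting. The size cannot be established, because the article gives no staff counts and no hospital rates. The −0.6 to +3.6 points above rest wholly on the listed assumptions, and the shift vanishes if the groups answer alike. Nothing in the article requires that hospital and primary care respondents never be combined. What is needed is that a combined figure is not the main answer to an objective about primary care. The correction is worth making because it is cheap and uses an item already collected.

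**What to change.** 1. In the Analysis plan, state that for objectives 1, 2, 4 and 5, and for the logistic model of correct identification, the main estimates use respondents from the primary healthcare teams, the linked Sexual and Reproductive Healthcare Programme and the linked social workers. Identify them by the work centre or department item.
2. Report hospital department respondents as a separate stratum. An all-respondent figure may be added as secondary.
3. In Data collection, keep a hospital/primary-care flag alongside the anonymised centre code. A two-level flag need not identify any centre.
4. Reconcile the Methods/design, Healthcare Workers and Selection of healthcare providers paragraphs, so that all three say whether hospital departments take part and in what role.

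Rewording the objectives to cover hospital staff would also remove the contradiction, but would move the study away from the primary care gap that the Background gives as its reason.

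The cost is a few sentences and one retained variable, with no new data collection. The drawback is a slightly smaller principal set, and so slightly wider intervals.
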